### Data Collection

For each participant, we will collect data for a period of 6 months following their entry into the study. The primary outcome is repeat HIV/STI screening, defined as the number of screenings participants receive over the 6-month observation period, an indicator of retention in the program and its effectiveness.

In addition, we will collect qualitative information about the experiences of participants and clinic staff, described below. We will use the following methods to collect our secondary outcomes.

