**Methods:**

The study consists of a formative research phase to develop the intervention and an implementation phase where the intervention is piloted in a controlled research setting. In the formative research phase, we use an iterative development process to design the intervention, including gathering information about the feasibility, acceptability, and expected effectiveness of potential game elements (eg, points, leaderboards, rewards). These activities include staff interviews, focus group discussions with members of the target population, and team meetings to strategize and develop the intervention. The final intervention is called Stick To It and consists of 3 components: (1) online enrollment, (2) Web-based activities consisting primarily of quizzes and a countdown “timer” to facilitate screening reminders, and (3) in-person activities that occur at 2 sexual health clinics. Participants earn points through the Web-based activities that are then redeemed for chances to win various prizes during clinic visits. The pilot study is a quasi-experimental study with a minimum of 60 intervention group participants recruited at the clinics, at community-based events, and online. We will compare outcomes in the intervention group with a historical control group consisting of individuals meeting the inclusion criteria who attended study clinics in the 12 months prior to intervention implementation. Eligible participants in the pilot study (1) are 18 to 26 years old, (2) were born or identify as male, 3) report male sexual partners, and 4) have a zip code of residence within defined areas in the vicinity of 1 of the 2 implementation sites. The primary outcome is repeat HIV/STI screening within 6 months.

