To test the potential of gamification for HIV/STI prevention, our 2-year study developed and will pilot Stick To It, an HIV/STI prevention intervention for YMSM (18-26 years of age) that incorporates elements of gamification. The objective of the intervention is to increase repeat HIV/STI screening, defined as screening at least every 3 months. HIV/STI screening is critical both as the gateway to HIV/STI treatment, which can lead to reduced onward transmission, and as a critical first step to access prevention strategies such as preexposure prophylaxis [34]. This paper describes the methodology and protocol of our study.

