The third component of the intervention involves the game of chance and takes place at the clinic. Participants also receive additional points for visiting the clinic for screening. Participants’ accumulated points are redeemable for prizes only at the clinic (for any reason, including screening or treatment). The redemption process works as follows. Gumball machines are located at each clinic. This was both the game of chance overwhelmingly preferred by the target population through our focus group testing and the most feasible to implement at the clinics. During their clinic visit, participants can draw between 1 and 5 gumballs, depending on their accumulated points. The number of points earned corresponds with the number of gumball draws available to the participant. The color combinations of the gumballs that are drawn determine the prize received. Points redeemed for gumball draws are deducted from the participant’s accumulated points at the time of redemption. The system of points and prizes was designed to result in an average prize cost of US $5 per screening visit. After screening, the countdown timer is reset for the next quarterly screening date. Multimedia Appendix 1 presents the points system and prizes used in the intervention. Multimedia Appendix 2 presents screenshots of the intervention website. Figure 2 shows a schematic of the final intervention design.

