#### In-Clinic Recruitment

Clinic staff will identify eligible individuals who visit the clinics for screenings, treatment, or other purposes and will inform them of the study and invite them to participate. In addition, placing flyers in the clinics and displaying the gumball machines in examination rooms will facilitate conversations about the intervention with potential participants. Those who are interested will be given a handout directing them to the intervention website, where they will be invited to complete an eligibility questionnaire and, if eligible, provide consent to participate in the study. Those with a smartphone will be invited to sign up while still at the clinic. Those who are eligible and provide consent will enter the study.

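### The primary outcome is a raw count of screenings over 6 months, which can rise without more men screening every 3 months, the stated objective

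*Protocol article*

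**What the plan says.** The article describes the primary outcome or its target in four places, and they do not agree.

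- Introduction: "The objective of the intervention is to increase repeat HIV/STI screening, defined as screening at least every 3 months".
- Abstract, Methods: "The primary outcome is repeat HIV/STI screening within 6 months". This reads as yes or no.
- Study Design, power statement: the assumed control rate is the share of men with at least one repeat screening visit in 6 months, 50%, against 77% in the intervention group. This is a yes/no outcome.
- Data Collection: "The primary outcome is repeat HIV/STI screening, defined as the number of screenings participants receive over the 6-month observation period". This is a count, and the same sentence calls it an indicator of retention and effectiveness.

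Only Data Collection gives the measured outcome a formal definition. It sets no spacing between screenings and no upper limit. Data Analysis provides for both kinds of variable: prevalence ratios for binary outcomes, and ordinary least squares or zero-inflated Poisson regression for continuous and discrete ones.

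Two design features bear on what enters the count. On recruitment at the clinic: "Those with a smartphone will be invited to sign up while still at the clinic". On rewards: "Participants also receive additional points for visiting the clinic for screening".

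**The concern.** The objective concerns regularity and the defined outcome measures volume. A man who re-tests several times in the first weeks and then stops scores higher than a man who keeps to the quarterly schedule. A comparison of mean counts can therefore favour the intervention although no more men are screened in each quarter.

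Entry at the clinic adds an ambiguity. Observation runs from study entry, and some men enter by smartphone during a clinic visit. A test later that day falls after entry, and the definition does not say whether it is baseline or outcome. Historical controls come from medical records and had no enrolment step, so the two groups could be counted differently.

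The Discussion says the comparison should show whether there is an early signal and whether further study is warranted. A count that moves separately from quarterly screening could mislead that decision in either direction.

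**Working it through.** **1. The plan's own figure.** The only stated figure is for the yes/no form: 60 per group, 50% against 77%, 80% power. Significance level and sidedness are not stated; I assume two-sided 5%.

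- Mean proportion = (0.50 + 0.77)/2 = 0.635.
- Null standard error = √(2 × 0.635 × 0.365/60) = 0.0879.
- Standard error under the alternative = √((0.25 + 0.1771)/60) = 0.0844.
- Power = Φ[(0.27 − 1.96 × 0.0879)/0.0844] = Φ(1.16) = 87.7%.
- With continuity correction, or with Fisher's exact test: 83.2%.
- Smallest difference detectable at 80% power: 24.6 points uncorrected, 26.1 points corrected.

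The stated 27 points is slightly conservative, and nothing below depends on it. It does show that the pilot was sized for a yes/no outcome and not for the count in Data Collection.

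**2. The definitions applied to two hypothetical men.** Both are screened on the day of entry, and that screen is taken as baseline.

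| | Count | Any repeat | 3-month windows with a screen |
|---|---|---|---|
| Four screens in the first six weeks, none after | 4 | yes | 1 of 2 |
| One screen in each 3-month window | 2 | yes | 2 of 2 |

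The count ranks the first man higher, the yes/no form cannot tell them apart, and only the last column follows the objective.

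**3. Illustration of size.** The documents give no rate of early re-testing, so the rates here are assumptions.

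- Control counts are taken as Poisson with 50% of men having at least one screen (the rate in the power statement), so the mean is ln 2 = 0.693.
- A fraction f of intervention men make one extra screen in a window that already holds one, so quarterly coverage does not change.
- Rate ratio = (0.693 + f)/0.693.
- Approximate z = ln(rate ratio)/√(1/events₁ + 1/events₀), and the chance of a nominally significant increase is Φ(z − 1.96).

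| f | Rate ratio | Chance, 60 per group | Chance, 200 per group |
|---|---|---|---|
| 10% | 0.793/0.693 = 1.14 | 9% (z = 0.63) | 21% (z = 1.16) |
| 20% | 0.893/0.693 = 1.29 | 23% (z = 1.23) | 61% (z = 2.24) |

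At 10% and the minimum sample size the effect on formal significance is small. The 61% needs both the higher assumed rate and the maximum sample size.

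**4. Count and yes/no forms compared.** In both groups 50% of men have 0 screens, 30% have 1 and 20% have 2 (assumed), so the mean is 0.30 + 0.40 = 0.70. Extra closely spaced tests are added only among intervention men who already re-test.

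- One extra test in 25% of them: (0.70 + 0.5 × 0.25)/0.70 = 1.18.
- One extra test in all of them: (0.70 + 0.5)/0.70 = 1.71.

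In 20,000 simulated trials with 60 per group, the comparison of means was significant in 12% and 75% of trials respectively. The yes/no comparison stayed at about 5% in both. The inflation in this scenario is thus specific to the count.

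**The case against.** **It is a condensed article.** De-duplication and index-day handling are commonly left to a full protocol or analysis plan. That is fair for those details: the word repeat, and observation following entry, argue against counting the index test, and the power statement already speaks of visits. The entry-day route is therefore only a possibility. The point does not rest on it, because the definition that is stated differs from the objective that is stated.

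**At least every 3 months sets a maximum gap, not a cap.** This is true, and more frequent screening is compatible with the objective. But extra screens within a quarter are not evidence that the quarterly objective has been met.

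**Does the game drive early screens?** A reader might infer this from the points given for screening visits. The documents do not show it. The points schedule (Multimedia Appendix 1) is not shown and may limit it. "Points redeemed for gumball draws are deducted from the participant’s accumulated points at the time of redemption", so an early return tends to have less to spend. Points can be redeemed at a visit for any reason, so redemption needs no extra screen. New quizzes come every 3 weeks, and the timer and messages aim at the quarterly date. The reward is also modest: "The system of points and prizes was designed to result in an average prize cost of US $5 per screening visit".

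**Does early re-testing in both groups erode the stated power?** A reader might infer this too. The power statement's 50% and 77% are shares with at least one repeat visit and carry no minimum gap, so any early returns are already in them. Subtracting a further loss would count them twice.

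**It is a pilot.** The article says the analyses are likely underpowered and disclaims causal statements. That limits the consequences, but the choice of outcome still shapes the signal on which further study depends.

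**Conclusion.** The point holds as a mismatch between the defined primary outcome and the objective, made worse by a yes/no version in the Abstract and the power statement. Under the count, closely spaced re-tests raise the primary outcome with no gain in quarterly screening. Under the yes/no form the lack of a cap does not matter, but a single re-test soon after entry still counts.

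The size is unknown. The rate ratios of 1.14 and 1.29 rest on an assumed 10% or 20% of intervention men with one extra early screen, none in controls, and a control mean of 0.69. They show how sensitive the count is; they do not predict what will happen. The documents establish neither that the prizes cause early screening nor that the stated power is lost.

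**What to change.** Reconcile the four descriptions and name one primary outcome that matches the objective:

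- Count distinct screening dates, not tests.
- Treat any screen on the entry or index day as baseline, in both groups.
- Credit at most one screen per 3-month window, or report the share of men screened in each window.
- Apply the same rule to the historical controls, with an equivalent index date.
- Report the raw count and the share with at least one repeat visit as secondary or sensitivity analyses.

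Do not use a fixed 30-day gap from study entry. The timer is set from the last screening date entered at enrolment, and men may enrol online or in the community. A man last screened 11 weeks before entry is due about 13 − 11 = 2 weeks after it, and such a gap would discard his on-schedule screen. The loss would fall mainly on the intervention group, since controls are drawn from clinic records. If a minimum gap is wanted, for example because one early return visit can still fill the first window, it should run from the last actual screening date.

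The cost is a few sentences in the outcome definition and a date rule in the record extract, with no new data. Some genuine extra screens lose credit. The window is a convention, and a man who comes slightly late can fall across a boundary, which is why the other versions should be shown alongside.

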#### Postpilot Questionnaire, Administered to All Participants

A survey offered to all participants at the end of the study period will assess HIV/STI screening at other clinics (self-reported), barriers and facilitators to screening, and perceptions of the Stick To It intervention.

#### In-Depth Interviews

We will conduct up to 10 in-depth interviews with members of the clinic staff at the end the study period. We will gather detailed information on their perceptions of the intervention, including implementation challenges and successes, adaptability and integration with clinic operations, perceptions of effectiveness, and suggestions for future improvements.

We will also conduct in-depth exit interviews with up to 40 Stick To It participants from both locations. Our goal is to gather detailed information about whether the intervention was relevant, motivating, and culturally competent. Further, we hope to assess the level of satisfaction with the process of earning and redeeming points, the rewards used, and the program’s potential applicability to others. We will purposefully select a diverse group of men from different racial and ethnic groups and men who had different levels of engagement with the intervention. Topical areas will include the participant’s perception of HIV/STI risk, perceptions about and experience with HIV/STI screening, willingness to discuss sexual health with others, particularly motivating elements of the game, and any unexpected challenges or adverse events.

We will examine whether Stick To It was culturally appropriate, relevant, and nonstigmatizing for YMSM, with an emphasis on African American and Latino YMSM, who are disproportionately affected by HIV [41]. Thus, at the completion of the in-depth interviews, we will administer a short interviewer-administered survey that includes the validated 20-item Public Perception of Physician’s Cultural Competence Scale, which measures client perceptions of physicians’ cultural competence [42]. We will adapt the scale to also refer to the clinic staff involved in Stick To It, and the design of the intervention itself. In addition, given the issues of stigma and discrimination that may adversely affect health care access among YMSM, we will include questions adapted from the validated Experiences of Discrimination [43] scale and the Discrimination in Medical Settings Scale [44] to determine whether the intervention or its implementation was stigmatizing.

In-depth interviews will be conducted in English by trained staff and will follow standard procedures [45,46]. A semistructured interview guide will cover predetermined issues (to ensure systematic data collection), but the interviewer will be free to change the sequence and wording of questions to ensure that unexpected themes can emerge [47]. Interviews will be audio recorded, with participant’s consent, and later transcribed verbatim.

Figure 3 summarized our study design, screening and recruitment process, and data collection.

**Figure 3 figure3:**
[figure not shown]
Summary of study design, screening and recruitment process, and data collection.

### Data Analysis

For quantitative outcomes, we will first assess missing data, describe participant characteristics using frequency tables, and provide descriptive statistics (eg, means, standard deviations, medians, ranges, proportions) for the primary and secondary outcomes stratified by group. For the binary outcomes, we will compare the intervention and comparison groups by computing unadjusted and adjusted prevalence ratios and 95% confidence intervals using generalized linear models, such as log-binomial regression [48-50]. For the continuous and discrete outcomes, we will use ordinary least squares and zero-inflated Poisson regression (depending on the distribution of the outcomes) to determine the change in outcomes associated with participation in the intervention, before and after controlling for baseline characteristics. All regression analyses will include robust standard errors to adjust for heteroscedasticity and clustering. We will also perform a per-protocol analysis limited to participants that had a minimum level of engagement with the intervention during the study period (eg, ≥25th percentile of points earned during the game).

Qualitative data analysis will be conducted with ATLAS.ti (Scientific Software Development GmbH) following standard procedures [47,48]. In brief, we will combine inductive and deductive techniques to strengthen the validity of the coding system and our conclusions during the multistage analysis process [46-50]. Two researchers will independently review the transcripts and code according to broad, a priori, and emergent themes related to gamification theory and barriers and facilitators of regular screening. Interviewer notes capturing contextual details, quality, inconsistencies, and impressions will also be incorporated. Data reduction will be based on coding sorts of the most central themes (eg, engagement with the intervention) followed by a systematic analysis of related themes (eg, motivation, risk perception, stigma) using coding matrices to identify relationships [44,51]. To reduce threats to validity, we will solicit feedback on our hypotheses from participants (respondent validation) [52] and rigorously examine theoretical validity—whether the data are consistent or inconsistent with the underlying theoretical models [47].

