#### Final Intervention Design

The final intervention consists of 3 components: online enrollment, Web-based activities, and in-person activities that occur at the clinic. Participants earn points through the Web-based activities, which they then redeem for a chance to win prizes during clinic visits. All content was developed prior to the implementation phase of the intervention.

In the first component, participants go through an online enrollment process and introduction to the intervention. The enrollment process consists of answering study eligibility questions, providing consent to participate in the study, and answering basic demographic questions. The introduction to the intervention consists of reading a short tutorial, inputting the date of last HIV/STI screening—used to set the countdown timer for the next recommended screening—and being invited to answer a 5-question multiple-choice quiz on a topic related to sexual health. Quizzes include questions that test knowledge of sexual health information that members of the target population may value (eg, STI symptoms, treatment, transmission risk, and prevention strategies) and questions primarily intended to be humorous or whimsical. Participants earn points for each step of this process (except for providing consent).

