The second component, Web-based activities, occur on the intervention website (stick2it.org) and are intended to accomplish two primary goals. The first is to provide multiple reminders of the approaching quarterly screening date, which is accomplished through the prominent display of the countdown timer on the personalized webpage dashboard using a graphic presentation that was designed as part of the aesthetic theme of the intervention. The second is to provide participants the opportunity to accumulate points, which increases their chance of winning more valuable prizes at the clinic, thus increasing their motivation to receive quarterly HIV/STI screening. The online activities are primarily triggered by a series of short message service (SMS) text messages, inviting participants to visit the intervention website and complete various activities, such as taking the latest quiz, viewing their screening countdown timer, and inviting friends to join the intervention. Messages are sent with increasing frequency as the participant approaches their quarterly screening date, beginning with a 3-week interval, increasing to a 1-week interval. To complete each quiz, participants click a link in the SMS message directing them to their home page on the intervention website, where participants can also view their countdown timer. Points are awarded for answering the quiz questions, with additional points awarded for answering correctly. Participants are provided with an opportunity to take a new quiz every 3 weeks throughout the course of the intervention. In addition, participants earn points when they invite eligible friends who subsequently enroll in the intervention. Invited friends must meet all participant inclusion criteria.

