### Study Design

Owing to potential spillover effects between the treatment and control groups within local peer groups, we deemed a randomized design to be impracticable. Instead, our study will use a quasi-experimental study design with a historical control group consisting of eligible participants identified within the medical records of the same clinics over the 12 months prior to the intervention phase of the study. We preregistered the study (clinicaltrials.gov NCT02946164). All eligible individuals recruited at the clinics, at community-based events, and online will be assigned to the treatment group. We will recruit a minimum of 60 participants and a maximum of 200 participants into the treatment group and identify an identical number of individuals to serve as a historical control group. To our knowledge, this will be the first intervention using gamification to target YMSM for repeat HIV/STI screening. Accordingly, we chose a large sample size range as the upper bound, as it is not possible for us to predict what the demand will be for such an intervention among the target population.

Given the pilot nature of the study, the proposed analyses will likely be underpowered for formal testing purposes. Nevertheless, if we assume that half of the men in the comparison group will attend 1 or more repeat HIV/STI screening visits over 6 months of follow-up, with 60 men in each group, we will have 80% power to detect a minimum change of at least 27 percentage points (from 50% to 77%), which is comparable to the increase observed in an incentive-based intervention previously implemented by the community-based organization that operates the 2 clinics in our study [39].

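### The example per-protocol cut-off ranks participants within the sample and sets no minimum of engagement, so men inactive after sign-up can qualify

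*Protocol article*

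**What the plan says.** Under Data Analysis, the per-protocol analysis is restricted to participants with a "minimum level of engagement with the intervention during the study period (eg, ≥25th percentile of points earned during the game"). No other criterion is given.

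Final Intervention Design describes where points come from:

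- **Enrolment and introduction.** "The enrollment process consists of answering study eligibility questions, providing consent to participate in the study, and answering basic demographic questions". A tutorial, entry of the last screening date and an invitation to a five-question quiz follow. "Participants earn points for each step of this process (except for providing consent").
- **Later quizzes.** "Points are awarded for answering the quiz questions, with additional points awarded for answering correctly". Inviting friends who then enrol also earns points.
- **Clinic visits.** "Participants also receive additional points for visiting the clinic for screening".

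On size, Study Design states: "We will recruit a minimum of 60 participants and a maximum of 200 participants into the treatment group". The point values are in Multimedia Appendix 1, which is not reproduced in the text at hand.

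**The concern.** A per-protocol set is meant to show the result among men who used the intervention. A sample percentile cannot do that, because what it tests is a man's position among the other participants and not what he did. The same score can pass in one sample and fail in another.

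Enrolment alone gives a positive score. If enough men stop after sign-up, the 25th percentile falls among them and some are counted as engaged. If everyone engages well, men are still removed for falling short of a minimum that they plainly met. A threshold whose meaning shifts with the sample also gives a later, larger study little to reuse.

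**Working it through.** **Inputs.** From the article: the percentile rule, the sources of points, 60 to 200 participants, and the planning rates of 50% and 77% for repeat screening (Study Design). Assumed: the share f of men with no website activity after sign-up, the point values, and screening rates of 77% in active men and 50% in both inactive men and controls. The article states no size for the per-protocol set, so there is no figure of its own to reproduce.

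**1. Share kept.** Without ties, points at or above the sample 25th percentile keep 45 or 46 of 60 men (75.0% to 76.7%) and 150 or 151 of 200 (75.0% to 75.5%). Over eight quantile definitions and every n from 60 to 200, the lowest share is 74.2%. Ties at the cut-off only raise it. With all 60 men fully active and no ties, 14 or 15 are still dropped.

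**2. Inactive men in the set, screening points left out.** If inactive men rank lowest and exactly 75% are kept, their share of the set is max(0, f − 0.25) / 0.75.

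| f | Sign-up scores differ (n = 60) | Sign-up scores equal (n = 60) |
|---|---|---|
| 25% | 0 of 15 inactive men kept | 0 of 15 kept |
| 30% | 3 of 18 kept; 3/45 = 6.7% of set | 18 of 18 kept; set is all 60 |
| 50% | 15 of 30 kept; 15/45 = 33.3% of set | 30 of 30 kept; set is all 60 |

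When each man's activity is drawn at random, equal sign-up scores give 94%, 99.7% and 100% kept at 30%, 40% and 50% inactive. Scores that vary with the introductory quiz give 79% to 83% kept, with 12% to 40% of the set inactive.

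**3. Adding screening points, as the article describes.** An inactive man who screens leaves the sign-up floor. With half of inactive men screening, the share still on the floor is f × (1 − 0.50). For it to exceed 25%, f must exceed 0.25 / 0.50 = 50%. In a sample of 60, the usual interpolated percentile is the 1 + 0.25 × 59 = 15.75th lowest score, so everyone is kept only if at least 16 men are tied on the floor. The binomial probability of that, with equal sign-up scores, is:

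| f | Floor share | P(at least 16 of 60) |
|---|---|---|
| 30% | 15% | 1.4% |
| 40% | 20% | 13% |
| 50% | 25% | 43% |
| 60% | 30% | 76% |

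**4. Effect on the estimate.** The full-sample difference is 0.77(1 − f) + 0.50f − 0.50 = 0.27(1 − f). If a quarter of men were dropped and all of them were non-screeners, the per-protocol difference would reach a ceiling of [0.50 + 0.27(1 − f)] / 0.75 − 0.50.

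| f | Full sample | Ceiling |
|---|---|---|
| 30% | 18.9 points | 0.689/0.75 − 0.50 = 41.9 points |
| 40% | 16.2 points | 0.662/0.75 − 0.50 = 38.3 points |
| 50% | 13.5 points | 0.635/0.75 − 0.50 = 34.7 points |

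Simulations at n = 60 lie between these two columns:

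- Assumed screening award of 100 points, 30% to 50% inactive: 10% to 43% of the set inactive; per-protocol difference 23 to 31 points against 13 to 19 in the full sample.
- Awards of 50 to 300 points, equal sign-up scores, 30% to 40% inactive: about 80% to 84% kept; 15% to 29% of the set inactive; difference about 30 to 36 points against 16 to 19.
- Other assumed awards gave up to 41 points at 30% inactive.

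The upward shift comes from screening visits counting towards the score, which favours men who had the outcome. The percentile form is what lets inactive men in.

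**The case against.** **The percentile is introduced as an example, in a condensed article.** The final definition may well sit in a fuller document. That lowers the weight of the point. It does not remove it, because the one criterion offered is of a kind that cannot express a minimum.

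**The inactive share is unsupported.** This stands. The article gives none; the nearest remark, on uptake, is that "it is not possible for us to predict what the demand will be for such an intervention among the target population". At about 20% or fewer inactive, inactive men are only a small part of the set.

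**Poor engagement would show anyway.** Quiz counts and invitations are reported as secondary outcomes, so a reader would see low use beside any per-protocol result. This is a fair mitigation, though it does not make the restricted set one of engaged men.

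**The stakes are low.** The analysis is supplementary, in a pilot that calls itself underpowered and disclaims causal statements.

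**A stronger reading to resist.** A reader might infer that, when engagement is poor, the rule returns nearly the whole sample, so that the per-protocol estimate copies the diluted full-sample one and agreement is mistaken for robustness. The article does not support that as the general case. Screening visits earn points, which lifts many inactive men off the floor, and the introductory quiz probably makes sign-up scores differ. Near-complete collapse needs tied sign-up scores and either no screening points or well over half of men inactive. Short of that, the two estimates tend to diverge, with the per-protocol one higher.

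**Conclusion.** The point holds in limited form. That the rule keeps about 75% or more of participants at any level of engagement, and drops about a quarter of a fully engaged group, follows from the definition of a percentile and needs no assumption beyond few ties. That men inactive after sign-up enter the set is conditional: broadly, on more than about a quarter of the sample being inactive. The figures of 10% to 43% of the set inactive and an inflated difference rest on 30% to 50% inactivity, assumed point values, and the 50% and 77% screening rates applied to inactive and active men. It is a minor improvement to a supplementary analysis and does not touch the primary comparison.

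**What to change.** Replace the percentile example with an absolute threshold, fixed before the data are seen, on website use after enrolment. One suitable form is at least one SMS-linked quiz completed after the enrolment quiz. Neither enrolment-step points nor screening-visit points should count towards it. Report the proportion of participants who meet it as an engagement result, and label the restricted comparison exploratory.

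The cost is about one sentence in the analysis section; completed quizzes are already a secondary outcome, so no new data are needed. The drawback is that the size of the per-protocol set is no longer guaranteed and may be small if engagement is low.
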